**FIGURE 3 F3:**
[figure not shown]
Surface electrode placement locations. **(A)** Right orbicularis oris. **(B)** Left masseter. **(C)** Right submental muscle group; Left infrahyoid muscle group (31).

##### Quality of living: Swallowing *of Life Questionnaire*

2.9.2.2

Patients complete the Quality questionnaire under physician guidance after fully understanding each question’s format. The SWAL-QOL (33) comprises 44 items organized into 10 dimensions (totaling 30 items): general burden, appetite, mealtime duration, food selection, communication, fear, mental health, social functioning, fatigue, and sleep, plus a separate 14-item symptom frequency assessment scale (34). Administering the SWAL-QOL before and after treatment provides clear, intuitive measurement of quality-of-life improvements, with higher scores indicating better quality of life (35).

##### Neurological deficit: National *of Health Stroke Scale*

2.9.2.3

The National InstituteInstitutes of Health Stroke Scale (NIHSS) (36) assesses neurological deficit severity through 15 evaluation items: level of consciousness, gaze, visual fields, facial palsy, motor function of upper and lower limbs, limb ataxia, sensory function, language, dysarthria, and extinction/inattention (37). The scale ranges from 0 to 42 points, with higher scores indicating greater stroke severity (38). Trained researchers score each item based strictly on the patient’s initial responses without providing cues or prompts (37).

##### Swallowing safety and efficacy: Fiberoptic Endoscopic Evaluation of Swallowing

2.9.2.4

FEES serves as a well-established and reliable tool for assessing swallowing impairment and guiding behavioral interventions (39). During the procedure, a clinician passes a flexible fiberoptic endoscope transnasally to directly visualize the structural integrity of the oropharynx and larynx, while dynamically observing key physiological events such as bolus transit, glottic closure, and laryngeal elevation. These observations provide a quantitative basis for grading the severity of swallowing dysfunction. Swallowing safety is evaluated using the Penetration-Aspiration Scale (PAS) (40), whereas swallowing efficacy is measured with the Yale Pharyngeal Residue Severity Rating Scale (YPRSRS) (41). Both instruments offer objective metrics that help minimize subjective assessment bias and support the development of individualized treatment plans.

To detect silent aspiration during Fiberoptic Endoscopic Evaluation of Swallowing (FEES), the endoscope will be maintained in position for an extended observation period of 45 s following each bolus swallow, allowing for the active capture of delayed aspiration events. Even in the absence of immediate aspiration, the presence of subglottic residue—observed as retained material or contrast-stained liquid below the vocal folds—will be documented as indirect evidence of silent aspiration. For precise quantification, the Penetration-Aspiration Scale (PAS) will be applied with specific grading annotations; for instance, “PAS 5 with thin liquids” will be recorded instead of the generic “PAS 5.” Furthermore, the incidence of silent aspiration will be statistically analyzed separately, and its association with the Functional Oral Intake Scale (FOIS) scores will be examined to reduce bias in therapeutic outcome evaluation.

##### Treatment expectation assessment: Treatment Expectation Questionnaire^1^

2.9.2.5

Treatment expectations will be assessed using the abbreviated Treatment Expectation Questionnaire (TEX-Q) (42), a 15-item instrument comprising six subscales. This measure was adopted due to the lack of validated tools for assessing treatment expectations in the context of stroke rehabilitation within the Chinese population. Higher scores on the TEX-Q indicate stronger expectations toward the assigned intervention. At baseline, participants in both the acupuncture and rehabilitation control groups will complete the treatment-specific version of the questionnaire, while the healthy control group will be exempt from this assessment. This baseline expectation evaluation will be conducted concurrently with other baseline measurements, immediately after enrollment but prior to the initiation of any treatment.

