### Study design

2.2

This is a multicenter, open-label, randomized controlled trial. A total of 115 participants will be enrolled, including 100 PSD patients to be randomly allocated in a 1:1 ratio to either the experimental group or the rehabilitation control group, and 15 additional participants will serve as the healthy control group. The study period will include baseline observations and 4 weeks of treatment. The clinical efficacy of acupuncture intervention will be assessed using functional assessment scales on day 15, day 30 during treatment, and at 30 and 60-day follow-ups after treatment completion.

This clinical trial adheres to the Consolidated Standards of Reporting Trials (CONSORT) guidelines (12) and complies with the Standards for Reporting Interventions in Clinical Trials of Acupuncture (STRICTA) (13) to ensure methodological rigor in acupuncture-specific interventions. The study design flowchart is presented in Figure 1.

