### Sample size, randomization, and blinding

2.7

The primary efficacy outcome is the FOIS score. As neither our team nor previous studies have used this measure to assess acupuncture efficacy for post-stroke dysphagia, it is not possible to determine an appropriate effect size from existing data. A review of similar studies has revealed that after 4 weeks, the FOIS score difference from baseline was 1.31 (rehabilitation training group) vs. 0.31 (sham training group), with a standard deviation of 1.09 (16). This value will be used as the expected effect size for this trial, and sample size calculations will be conducted based on a superiority trial design (17). These parameters (μA = 1.31, μB = 0.31, σ = 1.09, α = 0.05, power = 0.8, δ = 0.39) were applied in a superiority design with 1:1 allocation. After calculation, nA = nB = 40. Considering a 20% dropout rate, this study is expected to enroll 100 patients.

Randomization will use computer-generated numbers to allocate patients equally to acupuncture or rehabilitation groups. A stratified block randomization design will be employed. An independent statistician will generate all random sequences in SPSS 25.0, with study center and baseline FOIS as stratification factors, block lengths of 4 and 6 randomly interleaved, and the seed number set to 20240420. Allocation concealment will be implemented through sequentially numbered, opaque, sealed envelopes kept by a research coordinator who has no conflicts of interest with the study team. After participants have completed baseline assessments and provided written informed consent, the responsible physician will open the corresponding envelope on-site to reveal the allocation. The statistician generating the random sequence will operate independently of the coordinator handling allocation concealment. Neither patients nor physicians will know the allocation in advance. All participants will be followed for 90 days.

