#### Analysis adjusting for treatment expectations

2.12.3

For the primary efficacy outcome (FOIS) and key secondary subjective measures (SWAL-QOL, PRO), analysis of covariance (ANCOVA) or mixed-effects models will be employed, with the total baseline treatment expectation score included as a covariate to control for its potential influence on treatment outcomes.

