This study incorporates significant methodological improvements over previous research, most notably through the inclusion of a healthy control group to establish baseline physiological parameters, enabling stronger mechanistic investigations and enhanced pathological characterization. By conducting the study at two centers while minimizing multi-center coordination challenges—including inter-site variability in equipment specifications, intervention protocols, and staff training standardization—we enhance methodological rigor. Despite the open-label design, this study incorporates multiple methodological safeguards to mitigate potential biases. Standardized assessments, third-party evaluators, and multimodal verification confined detection bias to an acceptable range. Performance bias was controlled by measuring baseline expectations with standardized scales and including these scores as covariates in efficacy analyses. Pre-specified subgroup analyses and thorough control of confounders minimized false-positive risks from data dredging while supporting evidence-based individualized care.

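### The FOIS model adjusts for expectation of the assigned treatment, a score that allocation itself can change, so the treatment effect loses the protection of randomisation

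*Protocol article*

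**What the plan says.** - **What is measured.** Section 2.9.2.5: "Higher scores on the TEX-Q indicate stronger expectations toward the assigned intervention". It adds that "participants in both the acupuncture and rehabilitation control groups will complete the treatment-specific version of the questionnaire".
- **When.** The same section says "This baseline expectation evaluation will be conducted concurrently with other baseline measurements", and places it "immediately after enrollment but prior to the initiation of any treatment". Neither phrase says before allocation.
- **When allocation is revealed.** Section 2.7: "After participants have completed baseline assessments and provided written informed consent, the responsible physician will open the corresponding envelope on-site to reveal the allocation".
- **Who knows the allocation.** Section 2.2: "This is a multicenter, open-label, randomized controlled trial".
- **How the score is used.** Section 2.12.3 specifies ANCOVA or mixed-effects models for FOIS, SWAL-QOL and PRO, "with the total baseline treatment expectation score included as a covariate to control for its potential influence on treatment outcomes". Section 2.12.5 lists the score again among the potential confounders for the primary and secondary efficacy outcomes.
- **What is claimed for it.** Section 3: "Performance bias was controlled by measuring baseline expectations with standardized scales".

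**The concern.** A covariate is safe in a randomised comparison when allocation cannot have affected it. Its mean is then equal between arms in expectation, and adjusting for it gains precision without moving the target. Expectation of the treatment one has just been told one will receive does not meet that condition. A patient who hoped for acupuncture and drew rehabilitation may score lower because of the draw, and the reverse is equally possible.

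The score also has a different object in each arm: acupuncture in one, training in the other. Comparing patients with equal scores therefore does not compare patients with equal prior expectation.

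The primary outcome and the two most subjective secondary outcomes are affected. The adjusted coefficient would be read as the effect of acupuncture against rehabilitation. It would in fact be that effect plus or minus an unknown amount created by the adjustment. Nor can one score taken before treatment remove differences in care or behaviour that arise during an open-label trial, so the claim about performance bias does not follow.

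**Working it through.** **1. The order of events.** Section 2.7 puts baseline assessments before the envelope. Section 2.9.2.5 puts the TEX-Q with the baseline measurements but has it ask about the assigned treatment. Both cannot hold. Table 4 lists randomization and TEX-Q in the same Day 3–0 column and does not settle the order. Taking the possible readings in turn:

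- *TEX-Q after the envelope:* the score is post-allocation and can be changed by allocation.
- *TEX-Q before the envelope, about one treatment:* it cannot be about the assigned arm, so section 2.9.2.5 is wrong as written.
- *Both versions completed before the envelope, only the assigned one used:* allocation still decides which score enters the model.
- *A score defined identically for all patients before the envelope:* this is sound, but the article does not describe it.

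**2. The plan's own figure.** Inputs from section 2.7: difference 1.31 − 0.31 = 1.00, SD 1.09, margin 0.39, α 0.05, power 0.8.

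n per arm = 2 × (1.645 + 0.842)² × 1.09² / (1.00 − 0.39)² = 39.5, so 40. Then 40 / 0.8 = 50 per arm, 100 in all. The stated figure is reproduced with a one-sided 0.05; a two-sided 0.05 would give 51 per arm.

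**3. Size of the shift.** With one covariate, ANCOVA gives

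adjusted effect = unadjusted effect − b × D,

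where b is the within-arm slope of FOIS change per SD of expectation (b = r × 1.09) and D is the difference in mean expectation, acupuncture minus rehabilitation, in SDs. Neither r nor D is in the article, so both are assumptions.

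- r = 0.2, D = 0.5: 0.2 × 1.09 × 0.5 = 0.109
- r = 0.3, D = 0.5: 0.3 × 1.09 × 0.5 = 0.164
- D = 1 doubles these to 0.218 and 0.327

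**4. Consequences at 40 per arm.** The standard error is √(1.09² − b²) × √(2/40) / √(1 − D²/(D² + 4)). Power is Φ((adjusted − 0.39)/SE − 1.645). For a covariate fixed before allocation, D is 0 in expectation. The last column gives the two-sided 5% rejection rate against zero when the true effect is 0.

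| b | D | Planned 1.00 estimated as | Power against margin | Power, pre-allocation covariate | False-positive rate |
|---|---|---|---|---|---|
| 0.2 | 0.25 | 0.95 | 0.75 | 0.82 | 5.5% |
| 0.2 | 0.5 | 0.90 | 0.66 | 0.82 | 6.9% |
| 0.3 | 0.5 | 0.85 | 0.60 | 0.83 | 9.5% |
| 0.5 | 0.5 | 0.75 | 0.49 | 0.88 | 20.1% |
| 0.5 | 0.8 | 0.60 | 0.23 | 0.88 | 40.3% |
| 0.3 | −0.5 | 1.15 | 0.93 | 0.83 | 9.5% |
| 0.5 | −0.5 | 1.25 | 0.99 | 0.88 | 20.1% |

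A slope of 0.5 corresponds to r = 0.5 / 1.09 = 0.46, so those rows are at the high end.

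**5. Check by simulation.** There were 40 patients per arm and 5,000 runs per setting. Expectation had no causal effect on FOIS; the score shared a prognostic trait with FOIS and was shifted by allocation. A true 1.00 was estimated as 0.86 (b = 0.3, D = 0.5) and 0.75 (b = 0.5, D = 0.5), while the unadjusted estimate stayed at 1.01 and 1.00. With a true effect of 0, the rejection rate was 9.8% (b = 0.3, D = 0.5) and 38.8% (b = 0.5, D = 0.8). The formula and the simulation agree.

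**The case against.** The best defence is that post-allocation timing is not proven. The score is called baseline, it is taken with the other baseline measures, and section 2.7 puts those before the envelope. The reference to the assigned intervention could be loose wording, and the form itself is not shown. It is true that the documents do not settle the timing. But the order in section 2.7 does not rescue the plan: a score about the assigned arm has its object chosen by allocation whenever it is collected, and no common score is described.

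Second, the article names no single primary model, and section 2.12.3 might be only an additional adjusted analysis. That is fair as far as it goes. However, sections 2.12.3 and 2.12.5 are the only places that give a general between-arm model for FOIS, and both include the score.

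Third, the size is assumed and could be zero. This stands: the shift vanishes if D = 0 or b = 0, and 0.11 to 0.16 is well below the 0.39 margin. Raters blinded to allocation (section 2.11) may weaken the link with FOIS, though less so for self-reported SWAL-QOL and PRO. The plan does nothing to make either quantity zero.

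Fourth, one might want the effect net of expectation. That is a mediation question with further assumptions. The protocol does not pose it and instead calls the score a confounder.

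Finally, the limitations paragraph of section 3 concedes a risk of performance and detection bias. That contradicts, rather than repairs, the statement that such bias was controlled.

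**Conclusion.** The concern holds and must be fixed. As written, the models for the primary outcome and the key subjective secondary outcomes adjust for a score whose object, and possibly whose value, depends on allocation. The timing statements in sections 2.7 and 2.9.2.5 also contradict each other. These points rest on the text alone.

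The size rests on assumptions. The working range is 0.11 to 0.16 FOIS points at a 0.5 SD shift and 0.22 to 0.33 at 1 SD, for correlations of 0.2 to 0.3, against a planned effect of 1.0 and a margin of 0.39. The bias works against acupuncture if its patients report the higher expectations, and in its favour if they report the lower, given a positive slope. Neither can be determined from the article.

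**What to change.** 1. Reconcile sections 2.7 and 2.9.2.5 by stating whether the TEX-Q is completed before or after the envelope is opened, and which treatment or treatments each patient rates.
2. For patients still to be enrolled, collect it before the envelope is opened, with every patient rating both treatments on identical forms. Use only those scores as covariates.
3. For data collected after allocation, or about the assigned arm only, remove the score from the FOIS, SWAL-QOL and PRO models in sections 2.12.3 and 2.12.5. Report the adjusted result as a labelled sensitivity analysis, with a note that the covariate may be affected by allocation.
4. Delete the Discussion sentence that performance bias was controlled this way.

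The sample size does not change. A true pre-allocation score would give power of 0.82 to 0.88 at 40 per arm for b = 0.2 to 0.5, against 0.80 unadjusted. The cost is a few minutes per patient where enrolment continues. Section 2.6 planned recruitment for April 2024 to June 2025, so the data may already be in hand. In that case only the analysis wording changes, and this should be settled before the outcome data are examined by arm.

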##### Self-evaluation: patient reported outcome

2.9.2.6

The patient-reported outcome (PRO) is a standardized questionnaire format typically administered at baseline, during treatment, and during post-treatment follow-up.^2^ It primarily assesses patients’ symptom burden, physical function, mental health, and quality of life, serving as key indicators to evaluate treatment impact on swallowing function and quality of life. These subjective measures complement objective clinical assessments such as the NIHSS (43).

#### Safety assessment

2.9.3

##### Analysis of adverse events

2.9.3.1

Treatment-related AEs include symptoms such as throat discomfort or pain, coughing, and aspiration pneumonia caused by the trial intervention or acupuncture. Serious adverse events (SAEs) refer to symptoms that result in hospitalization, persistent or significant disability, functional impairment, life-threatening conditions, or death (44). Additionally, there may be treatment-unrelated AEs that occur outside the treatment period (44).

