### Inclusion criteria

2.3

Patients are eligible for study inclusion if they meet all of the following:

(1)   Fulfill the diagnostic criteria for acute ischemic stroke as defined by the Chinese Guidelines for the Diagnosis and Treatment of Acute Ischemic Stroke (2023 Edition) (14), and have dysphagia confirmed by the Scottish Intercollegiate Guidelines Network (SIGN) recommendations (15).(2)   Age between 18 and 80 years.(3)   FOIS levels between 2 and 4.(4)   Stroke duration of 15–180 days.(5)   Infarction location in the cerebral cortex and subcortical regions.(6)   Patients or their legal guardians must fully understand the study procedures, provide written informed consent, and agree to participate.

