### Recruitment of study participants

2.6

The study will be conducted at two hospitals of Hunan University of Traditional Chinese Medicine (First and Second Affiliated Hospitals), with the Second Affiliated Hospital leading study design and implementation. PSD participants will be recruited from hospital wards/clinics (April 2024-June 2025), while healthy controls will be enrolled from the community during the same period.

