##### Management of adverse events

2.9.3.3

When subjects experience significant AEs, clinicians must document all details and implement appropriate interventions. For SAEs, clinicians should administer emergency measures until the patient’s condition stabilizes. If abnormal laboratory parameters are observed, continuous monitoring should be performed until values normalize, with consideration given to discontinuing observation. Following each acupuncture session, clinicians will document any adverse events (AEs) using an Immediate AE Record Form. The recorded information will include AE symptomatology, time of onset, duration, severity, temporal relationship to the intervention (intra- or post-intervention), association with swallowing actions, and preliminary attribution level. Three days after SAE management, the subject’s general condition should be reassessed with relevant laboratory tests as needed to ensure no impact on subsequent treatment processes and outcomes. Subjects who develop abnormal post-treatment values after having normal pre-treatment values should receive regular follow-up examinations until the follow-up period concludes (Figure 4).

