##### Safety analysis

2.9.3.4

Adverse events will be analyzed using standardized evaluation scales. An independent Safety Committee (SC) will be established, composed of five members with no conflicts of interest: a principal investigator, an acupuncture clinician, a rehabilitation medicine specialist, a statistician, and a patient representative from the stroke rehabilitation community. The SC will be responsible for reviewing and evaluating all safety data and adverse events collected during the trial. Its specific duties will include assessing cumulative serious adverse event (SAE) reports, verifying entries in the Immediate AE Record Form within 24 h, conducting routine reviews every 2 months, and performing expedited reviews of any SAE within 48 h to ensure trial integrity and protect participants’ rights and health. For statistical analysis, Fisher’s exact test will be employed for categorical data comparisons, while the Kruskal-Wallis H test will be utilized for analyzing ordinal categorical variables.

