##### Scope of adverse event reporting

2.9.3.5

In accordance with the CIOMS Guidelines for Adverse Event Reporting (45), this study will comprehensively collect and report all adverse events (AEs). The reporting will include the frequency, severity, and potential relationship to the intervention for every documented AE, thereby ensuring a complete representation of participant safety exposure throughout the trial period.

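### The SAE definition counts events that lead to hospital admission but not those that prolong a stay, so seriousness in ward patients rests on assessor judgement

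*Protocol article*

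**What the plan says.** Section 2.9.3.1 defines serious events by their outcome: "Serious adverse events (SAEs) refer to symptoms that result in hospitalization, persistent or significant disability, functional impairment, life-threatening conditions, or death". The sentence is worded as a list, with no catch-all item and nothing to mark the entries as examples. The same section names, among treatment-related AEs, "aspiration pneumonia caused by the trial intervention or acupuncture".

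Section 2.6 gives the setting: "PSD participants will be recruited from hospital wards/clinics". Section 2.3 sets the time window at entry: "Stroke duration of 15–180 days".

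Section 2.9.3.4 gives the Safety Committee's duties. For serious events these are assessing cumulative SAE reports and "performing expedited reviews of any SAE within 48 h". For AEs in general they are "verifying entries in the Immediate AE Record Form within 24 h, conducting routine reviews every 2 months". Section 2.9.3.3 says when the form is filled in: "Following each acupuncture session, clinicians will document any adverse events (AEs) using an Immediate AE Record Form". Section 2.9.3.5 commits the trial to collecting and reporting every AE by frequency, severity and possible relationship to the intervention.

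**The concern.** A patient already in hospital cannot be hospitalised by an event. The hospitalisation criterion therefore works for outpatients and is silent for inpatients unless prolongation of a stay also counts, and the definition does not say that it does. In a dysphagia trial this matters because aspiration pneumonia is an event the article itself anticipates, and lengthening a ward stay is one of its plausible consequences.

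Two things are at stake. One is oversight, since the guaranteed 48 h committee review attaches to SAE status alone. The other is the meaning of the reported SAE count, which could under-represent harm in ward patients and vary with care setting and assessor.

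**Working it through.** The article states no figure to reproduce, and the point turns on wording, so the check sets the sections side by side.

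**Step 1. Criteria listed in 2.9.3.1.** There are five: hospitalisation; persistent or significant disability; functional impairment; a life-threatening condition; death. Prolonged stay is absent, as is any item for other medically important events. No other section shown widens the list. Sections 2.9.3.2 and 2.9.3.5 cite the CIOMS guidelines, but for attribution and for the scope of AE reporting, not to define seriousness.

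**Step 2. One event in two settings.** Take an aspiration pneumonia that is neither life-threatening, disabling nor fatal.

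| Criterion in 2.9.3.1 | Outpatient, admitted because of it | Inpatient, stay lengthened by it |
|---|---|---|
| Results in hospitalisation | Met | Cannot be met; already admitted |
| Persistent or significant disability | Not met | Not met |
| Functional impairment | Assessor's reading | Assessor's reading |
| Life-threatening | Not met | Not met |
| Death | Not met | Not met |
| Classed as SAE | Yes | Only if functional impairment is read to include it |

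**Step 3. Can the functional-impairment item stand in?** It has no threshold of degree or duration. Read broadly, it would catch the inpatient event, for example where oral feeding has to stop. It could then also reach events that Table 3 grades only moderate, since that grade already involves adjusting daily activities such as cutting down on hard foods. Read narrowly, it misses the inpatient event. The text does not choose between these readings.

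**Step 4. What depends on the SAE label.** Under 2.9.3.4, the 48 h expedited review and the cumulative SAE assessment do. Under 2.9.3.3, so does the reassessment three days after the event has been managed.

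**Step 5. What still covers an event without the label.**
- The 24 h verification applies to entries on the Immediate AE Record Form. Section 2.9.3.3 describes that form only after acupuncture sessions. Its listed contents include severity and preliminary attribution, but not seriousness or effect on hospital stay.
- Table 3 grades severity. Nothing ties its top grade to SAE status or to the 48 h review.
- The two-monthly routine review and the commitment in 2.9.3.5 to report all AEs apply without restriction by arm.

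An unlabelled event recorded after an acupuncture session is thus checked within 24 h. For one in the rehabilitation arm, or in either arm during follow-up, the only committee review with a stated timing is the two-monthly one.

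**Step 6. Size.** The expected number of events whose classification is in doubt would be

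N × (share of patients who are inpatients when the event occurs) × (rate of stay-prolonging events that meet no other criterion).

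Only N = 100 randomised patients is given. The two other factors appear nowhere, so no number follows.

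**The case against.** The strongest reply has four parts.

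**Existing criteria and safeguards.** Functional impairment is on the list and may well catch a pneumonia that sets back a dysphagic patient. Every AE is to be recorded, and form entries are verified within 24 h. This stands in part. A reader might infer that the inpatient event is definitely not an SAE, or that any event without the label waits up to two months for review. The text supports neither. The first overlooks the functional-impairment item, and the second overlooks the 24 h check. What remains is that the first safeguard is discretionary and the second is described only for acupuncture sessions.

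**Condensation.** The definition is one sentence with a citation, the AE management flowchart (Figure 4) is not shown, and the full protocol may hold a fuller seriousness checklist. That cannot be ruled out. But the article does not leave the definition to another document. It states one, and the one it states is incomplete for patients recruited partly from wards.

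**Imbalance between arms.** A reader might infer that the gap biases the SAE comparison through an unequal inpatient mix. Inpatient status at enrolment is a baseline feature, and allocation is randomised 1:1 with stratification by centre (section 2.7), so no systematic imbalance in it is expected. The difference between arms that the text does show is in recording, because the form is tied to acupuncture sessions.

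**Setting.** The article does not say how many patients are inpatients. Entry runs to 180 days after stroke and clinics are also a source. The daily recording of swallowing care by a study nurse (Table 1) suggests ward care but does not prove it. This stands, and it is why the point is limited to what can happen.

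**Conclusion.** The point holds as a defect in a stated rule. The definition can class the same event differently by care setting, and for an inpatient it leaves the decision to an undefined term. The possible loss is SAE classification, inclusion in the cumulative SAE count and the guaranteed 48 h review. Recording as an AE is not lost. Protection is weakest in the rehabilitation arm and during follow-up.

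This rests on two assumptions: that some patients are in hospital when an event occurs, which ward recruitment makes likely, and that no fuller definition governs in a document not shown.

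The size is unknown. A reader might put in assumed rates: with stay-related pneumonia in 10% of patients and 50% to 80% of them inpatients, 100 × 0.10 = 10 events, of which 10 × 0.50 = 5 to 10 × 0.80 = 8 would miss the hospitalisation criterion. Neither rate is in the documents. The result would also count events missing that one criterion, not missed SAEs, because others may apply. It should not be used as an estimate.

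The point is modest in weight, but worth correcting because it concerns safety oversight and the remedy is small.

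**What to change.** In section 2.9.3.1, add *or prolongation of an existing hospital stay* after the hospitalisation criterion. State that the definition applies identically in both arms from randomisation to Day 90. The AE row of Table 4 already appears to run onward from baseline with no restriction by arm, so the observation schedule need not change. Carry the same phrase into the AE form, so that effect on hospital stay is recorded.

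The cost is one phrase in the protocol and on the form, and slightly more SAE reports for the Safety Committee. Treatment, sample size and the efficacy analyses are untouched.
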